##### Data analysis plan

All qualitative interview data will be transcribed, and if not in English, translated from Runyankore into English by a research assistant. Translated transcriptions will be compared with recorded data by the researcher (SM) to ensure their accuracy. Then, the two researchers (HK, SM) and the five research assistants who conducted in-depth interviews will read all the transcripts and code overarching themes using MAXQDA version 18. Then, data will be compared between dual-method users and non-users to identify problems and barriers to adapting dual-method use and how they were overcome by positive deviants with their unique practice.

#### Phase II: cluster randomized controlled trial

##### Sample, eligibility, and recruitment

The minimum required sample size for this trial is 588. It was calculated based on data from research on the effect of case management and peer education program on the uptake of dual- method use in the USA (odds ratio [OR] = 1.58, 95% confidence interval [CI] = 1.03–2.43) [32]. The less conservative effect size of 2.43 was used because this trial will include only women who have already used HECs, unlike the prior research which recruited adolescent girls regardless of their contraceptive use [32]. Then, an intraclass correlation coefficient (ICC) of 0.006 was considered [33, 34]. The ICC was adapted from a clinic-based condom use intervention in SSA [33]. The required minimum sample size was 760 after considering the ICC. Considering a 26% dropout rate, 960 participants will be recruited (480 participants in each arm) [22]. The power of the study was set at 80% and the significance level was set at 5%. Open Epi version 3 was used for the calculation.

Twenty health facilities will be purposively selected considering the size and rural/urban status. The same inclusion criteria as Phase I will be used for this intervention study, but if women have been practicing dual-method use in the 2 months before recruitment, they will be excluded. The same sampling method as Phase I will be used to recruit women at health facilities. Eighty women will be recruited from each of the hospitals and county-level health centers, and 40 from each of the sub-county-level health centers and parish-level health centers.

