The present study has several limitations. First, the success of the positive deviance approach depends on whether women practicing dual-method use or positive deviants can be found in the study area [24, 48]. Considering the prevalence of such people, the sample size can be too small and may need to be modified. Second, positive deviants are identified by the research team not by community members in this trial. Therefore, the effect of the intervention can be limited in mobilizing and empowering communities to adopt identified strategies, compared to the usual approach including self-discovery of positive deviants [24, 48]. Third, high attrition is anticipated, especially among women in the control arm, as all the interventions and follow-ups after recruitment and initial counseling are phone-based [11]. The present trial, therefore, calculated the sample size considering a relatively high attrition rate to offset potential losses to follow-up. Moreover, it will be minimized by building rapport with participants. For this, each participant will be contacted by the same positive deviant and/or research assistant for counseling and follow-up throughout the study period. Fourth, the outcomes will be assessed based on self-reports from participants and thus subject to response bias. Dual-method use can be over-reported while the incidence of STIs and unintended pregnancies can be under-reported due to social desirability bias. However, response bias will be minimized by assuring each participant of confidentiality of responses at the enrollment. Lastly, findings of the present study might lack external validity to other locations as it will focus on one particular community under the positive deviance approach [48]. In the present study, participants will be recruited in only public health facilities; thus, findings from this study may not be generalized to all women using HECs. To apply findings and the interventions developed in the present study to other areas and populations, further research will be necessary to assess its effectiveness in a given context.

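### Recruiting 960 women leaves about 710 after the planned 26% dropout, 50 short of the plan's own minimum of 760; the text needs correcting, but the power loss is small

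*Protocol article*

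**What the plan says.** The section on sample, eligibility and recruitment for Phase II gives the calculation as a chain of totals.

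- Before clustering: "The minimum required sample size for this trial is 588". The effect is an odds ratio of 2.43, the upper confidence limit of a US study whose estimate was 1.58. No control-arm rate is given for this step.
- Clustering: "Then, an intraclass correlation coefficient (ICC) of 0.006 was considered", and then "The required minimum sample size was 760 after considering the ICC".
- Dropout: "Considering a 26% dropout rate, 960 participants will be recruited (480 participants in each arm".
- Error rates: "The power of the study was set at 80% and the significance level was set at 5" per cent.
- Facility sizes: "Eighty women will be recruited from each of the hospitals and county-level health centers, and 40" from each of the lower-level centres, with 20 facilities in all, 10 per arm.

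The limitations part of the Discussion says that high attrition is expected, particularly in the control arm, and that the trial "calculated the sample size considering a relatively high attrition rate to offset potential losses to follow-up". The inflation formula is not printed anywhere.

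**The concern.** The 760 is presented as the number required, and the 960 as that number after allowing for 26% dropout. So 960 less 26% should come back to about 760, and it does not. A trial that met its recruitment target and lost exactly the predicted share of women would still end below its published minimum.

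The clustering step has a related problem. The cluster size implied by going from 588 to 760 is not the size that the plan recruits or expects to retain, and the facilities are deliberately unequal. The 760 and the 960 therefore rest on different pictures of the same 20 facilities.

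At stake are the stated 80% power and the claim in the limitations that the sample size allows for attrition. Readers of the results will judge achieved enrolment and follow-up against 760, 960 and 80%.

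**Working it through.** **Inputs from the protocol article:** 588 before clustering; ICC 0.006; 760 after clustering; dropout 26%; 960 recruited; 20 facilities of 40 or 80 women; odds ratio 2.43; power 80%; significance level 5%.

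**1. Reproducing 960.** 760 x 1.26 = 957.6, which rounds up to 960. Division by the retained fraction gives 760/(1 - 0.26) = 1,027.03 (1,028 if rounded up to 514 per arm). So 960 is consistent with multiplying by 1 + dropout and not with dividing by 1 - dropout. This is an inference, because the formula is not shown. The next step does not depend on it.

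**2. What 960 delivers.**
- Retained at 26% loss: 960 x 0.74 = 710.4.
- Shortfall: 760 - 710.4 = 49.6 women, or 6.5% of 760.
- Largest dropout at which 760 is kept: 1 - 760/960 = 20.8%.

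**3. Cluster size behind the 760.** The design effect is 760/588 = 1.2925. Setting 1 + (m - 1) x 0.006 = 1.2925 gives m = 49.75, about 50 analysed women per facility. The plan implies 960/20 = 48 recruited and 710.4/20 = 35.5 retained.

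**4. Facility sizes.** With 20 facilities of 40 or 80, only 4 of 80 and 16 of 40 give 960. The mean is 48 and the variance is (4 x 32² + 16 x 8²)/20 = 256, so CV² = 256/48² = 0.111.

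**5. Effective size of 710.4 women under three design effects.**

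| Design effect | Value | Effective size |
|---|---|---|
| The plan's, held fixed | 1.2925 | 710.4/1.2925 = 550 |
| Retained size, unequal: 1 + (1.111 x 35.52 - 1) x 0.006 | 1.231 | 710.4/1.231 = 577 |
| Retained size, equal: 1 + (35.52 - 1) x 0.006 | 1.207 | 710.4/1.207 = 588.5 |

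**6. A consistent chain.** For unequal facilities, the retained N must satisfy N = 588 x [1 + (1.111 x N/20 - 1) x 0.006]. The solution is N = 727, and 727/0.74 = 982.4, so 983 recruited. With equal facilities the same equation gives about 710 retained and 709.7/0.74 = 959 recruited.

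**7. Power for an odds ratio of 2.43** (two-sided 5%, normal approximation for two proportions). The control rate is an assumption. At 5% (intervention 11.3%), the Kelsey formula gives 293.06, hence 294 per arm and 588 in total, so 5% reproduces the plan's starting figure. The 7% is the prevalence that the article uses to size Phase I.

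| Effective size | Control 5% | Control 7% |
|---|---|---|
| 550 | 77.6% | 88.3% |
| 577 | 79.6% | 89.8% |
| 588 | 80.3% | 90.3% |

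**The case against.** The strongest reply is that 960 is nearly enough, because the 760 is itself too high for the clusters that will be analysed. With equal facilities, 26% loss leaves an effective 588.5, which just meets 588. With the planned 40 and 80 split the consistent requirement is 727, so the gap is about 17 retained women or 23 recruits, not 50 and 67. This stands, and it is why the severity is modest. It does not rescue the text, which names 760 as the minimum and gives no lower figure.

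A second reply is that outcomes are collected at 2, 4, 6 and 8 months and modelled at each follow-up, so women lost late still contribute earlier outcomes. The article does not tie the 760 to month 8. That is a fair limit on what 710 means, but the plan's own allowance treats 26% as lost from the required number.

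Three stronger readings are tempting and are not supported:

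- A reader might infer that power falls to about 75%. That figure needs a t reference with 18 degrees of freedom, which the Data analysis section does not name. On that reference the full 588 would also give only about 76%, so most of the drop comes from having 20 clusters and not from the dropout step.
- A reader might take the limitations to say that attrition is fully offset, or that a 26% loss is likely. The sentence claims neither: it speaks of offsetting potential losses and gives no size for the attrition expected.
- A reader might state as fact that the authors multiplied by 1.26. The numbers point that way, but no formula is printed.

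**Conclusion.** The sample size chain is wrong as written. By the plan's own figures, 960 recruits with 26% dropout leave about 710 women, 50 below the stated minimum of 760. That result uses only printed numbers, and nothing else in the article resolves it. The clustering step is also out of line with the facility sizes that the plan fixes.

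The consequence is small. The effective size is 550 to 588 against a required 588, and the loss of power at an assumed 5% control rate is between nil and about 3 percentage points. If the control rate were 7%, power would stay near 88% to 90% throughout. The power figures rest on the ICC of 0.006, the odds ratio of 2.43, a control rate that the article does not give, and loss spread evenly over facilities. The recruitment target does not need to change on this ground; the text does.

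**What to change.** Keep 960 and correct the sample size paragraph:

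1. Show the chain in order: 588, then the design effect at the retained and unequal facility size, then division by 0.74. For an effective 588 this gives about 727 retained and 983 recruited.
2. State that 960 is nevertheless the target, that about 710 women are expected after 26% loss, and that 760 is kept only up to 20.8% dropout.
3. Give the effective size as about 550 to 588, naming the design effect used for each figure.
4. State the control rate behind 588 and the resulting power for an odds ratio of 2.43: about 77.6% to 80% if the rate is 5%, and about 88% to 90% if it is 7%.
5. In the limitations, keep the sentence on attrition but qualify it: the allowance covers part of the planned loss when measured against 760, and nearly all of it once the design effect is recomputed at the retained size.

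The cost is a rewording and, at a 5% control rate, a slightly less favourable power statement. No additional women and no change to design or analysis are needed. Should the sponsor prefer to keep 760 as a firm minimum, the alternative is to recruit about 1,028 women, 68 more than planned.

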##### Randomization

To minimize contamination across individuals, the C-RCT approach will be adopted [35]. The 20 health facilities will be stratified based on the level of health facilities and urban/rural status and randomized to the intervention (n = 10 facilities) or control arm (n = 10 facilities) (1:1 allocation ratio), using a computer random number generator by the principal investigator (HK). The participants will be given the intervention that the facilities they were recruited at were allocated to.

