#### Phase I: identify positive deviants

##### Sample size, eligibility, and recruitment

In Phase I, 150 women will be interviewed. This is based on the assumption that at least 7% of women would practice dual-method use [13] and at least 10 women who are considered as a positive deviant would be identified.

To be eligible for joining this study, participants should have the following characteristics: (1) women; (2) aged 18–49 years; (3) sexually active; (4) using HECs at the time of recruitment; (5) have a desire to avoid pregnancy for 12 months from recruitment; (6) have a husband or live-in sexual partner; and (7) have access to a valid phone number.

Being sexually active is defined as having had sexual intercourse in the 3 months before the study [13]. Pregnant women and women who are infertile for other reasons will be excluded from this study. Health workers, including community health workers, political and religious leaders, and teachers will also be excluded because they may not represent communities or be influenced by their occupations and social status.

For sampling, five health facilities will be selected purposively. Then, five trained female research assistants will approach female clients in the family planning sections of the selected health facilities. The first client will be selected randomly at each clinic and then every third client will be informed about the opportunity to participate in this study. If they are interested in participating, the research assistants will ask screening questions using a pretested questionnaire to check their eligibility for the study. This process will be repeated until the required sample size is met.

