##### Intervention

The intervention will consist of a series of counseling and participatory workshops, planned based on the unique practice identified in Phase I. On the day of enrollment, women in the intervention arm will receive dual-method counseling with a tool developed based on the practice identified in Phase I, in addition to regular family planning counseling with an existing counseling tool [36]. The dual-method counseling will be conducted for 20–40 min by trained research assistants.

Two weeks after enrollment, women in the intervention arm will be invited for a 1-day participatory learning workshop (5 h) at the same health facilities where they were recruited. Women may decide whether to participate. The workshop will be facilitated by research assistants and positive deviants, using a training protocol developed after Phase I. It will include simulations and role-plays for successful communication about using a condom with their partners and a group discussion regarding family planning and HIV/STI risk.

Bi-monthly telephone counseling will be provided by positive deviants three times (3, 5, and 7 months after enrollment). Each counseling session will take 10–20 min and aim to remind women of the risk of unintended pregnancies and HIV/STIs and strengthen their capacity to communicate using a condom with their partners. The 2-month intervals can allow women to reflect on counseling messages, discuss the use of condoms with their partners, and put it into practice. Positive deviants, therefore, can provide more effective counseling tailored to participants’ individual needs through understanding their situation.

Women in the control group will be provided regular family planning counseling including dual-method use for 10–30 min by trained research assistants using the same existing tool on the day of enrollment [36]. Moreover, refresher training will be provided bi-monthly on family planning and HIV/STI risk via phone, by research assistants three times (3, 5, and 7 months after the enrollment).

Condoms will be provided for free, regardless of the allocation at the selected health facilities. Before the intervention starts, the research assistants will receive a 2-day training session about the contents of the existing counseling tool by health professionals [36].

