##### Data collection

On the day of enrollment, all women will be interviewed using a pretested structured questionnaire to identify basic baseline characteristics. They will then be followed up via phone bi-monthly for 8 months to assess how the intervention influences dual-method use and pregnancy and STI incidence (2, 4, 6, and 8 months after enrollment). All interviews will be conducted by trained female research assistants using an interview guide in either English or Runyankore. All data will be entered using EpiData version 4.6.

All participants will be given some incentives worth 10,000 UGX (equivalent to US$3) for their time and participation in the study after the initial interviews. Participants who participate in the learning workshop will receive 20,000 UGX (equivalent to US$6) for transportation.

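### A facility's arm can be known when nearly all its women are screened and enrolled, and neither the sampling rule nor the stated effect model protects against selective enrollment.

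*Protocol article*

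**What the plan says.** **Allocation.** Twenty facilities are stratified by level and urban/rural status and randomized 1:1. There is no individual allocation: "The participants will be given the intervention that the facilities they were recruited at were allocated to" (Protocol article, Randomization).

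**Delivery.** The Intervention section states: "On the day of enrollment, women in the intervention arm will receive dual-method counseling". It adds: "The dual-method counseling will be conducted for 20–40 min by trained research assistants". Control women receive the regular counseling "by trained research assistants using the same existing tool on the day of enrollment".

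**Recruitment.** For Phase II, "The same sampling method as Phase I will be used to recruit women at health facilities" (Sample, eligibility, and recruitment). In Phase I the first client is chosen at random and every third client is then informed. "If they are interested in participating, the research assistants will ask screening questions using a pretested questionnaire", and this is repeated until the required number is reached. Phase II sets quotas of 80 or 40 women per facility, depending on its level.

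**Eligibility and outcome.** Women must wish to avoid pregnancy for 12 months. In Phase II, women who practiced dual-method use in the previous 2 months are excluded. The primary outcome counts only the top answer on a four-point condom-frequency scale, together with use of a highly effective contraceptive.

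**Analysis.** The Data analysis section gives a mixed-effects logistic regression with a random effect for clusters, then Models 1 to 6 to find predictors. It also compares background characteristics between arms. The limitations in the Discussion cover self-report, attrition and external validity, but not selective enrollment.

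**The concern.** Randomizing facilities makes the facilities comparable. It makes the enrolled women comparable only if enrollment does not depend on the arm. Where the arm can be known at the time of recruitment, the way the study is presented, the way a screening answer is recorded and a woman's own decision can all vary with it.

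The outcome makes this trial sensitive to such variation. A woman who gives either of the two intermediate answers on the condom scale is not a dual-method user by the plan's definition, so she is eligible. She is also only one or two steps from meeting the primary outcome. If one arm enrolls more of these women, the arms differ in later dual-method use before any intervention effect. Because each facility recruits to a fixed quota, women who decline are replaced, and differential acceptance would not show in the enrolled numbers.

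**Working it through.** No figure in the plan is at issue. The main check sets the sections side by side; the arithmetic only illustrates size.

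**Is the arm knowable at recruitment?**
1. A woman's arm is her facility's arm (Randomization).
2. Arm-specific counseling is given on the enrollment day (Intervention), so a facility's arm must be settled by the counseling step of its first enrollee.
3. Each facility delivers one arm only. From the second enrollee on, anyone who has seen the first visit can know the arm. If recruiting and counseling staff at a facility are not kept apart, at most 20 of 960 women (2.1%) could be recruited in ignorance of it.
4. Screening and counseling are both assigned to research assistants, and no separate recruiter is named.

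**Does anything else close the gap?**
- Sampling with a random start and every third client fixes who is informed, not who accepts.
- A pretested questionnaire standardizes the questions, but the answers remain self-reports recorded by staff who may know the arm.
- A baseline comparison can show measured imbalance; it does not correct it.
- The effect model names a cluster random effect. Models 1 to 6 name demographics, residence, contraceptive type, partner variables and perceived risk, but not baseline condom frequency.

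**Illustration A (assumed inputs, no true effect).** Control uptake is taken as 5%. The plan does not state a rate; with OR 2.43, 80% power and two-sided 5%, a rate of 5% gives 584 women, close to the plan's 588. Assume 10% of control enrollees are already inclined to use condoms and adopt at 20%, and the rest adopt at 3.33%: 0.10 × 0.20 + 0.90 × 0.0333 = 0.050.

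For inclined share *s* in the intervention arm, p₁ = 0.20*s* + 0.0333(1 − *s*) and OR = [p₁/(1 − p₁)] / [0.05/0.95].

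For the error rate, the analyzed number per arm is 480 × 0.74 = 355.2, or 35.52 per facility. The design effect is 1 + (35.52 − 1) × 0.006 = 1.207, so the effective number is 355.2/1.207 = 294 per arm. With z = (p₁ − p₀)/√{[p₀(1 − p₀) + p₁(1 − p₁)]/294}, the rejection rate is Φ(z − 1.96) + Φ(−z − 1.96).

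| *s* | p₁ | Spurious OR | z | Rejection rate |
|---|---|---|---|---|
| 0.10 | 5.0% | 1.00 | 0 | 5.0% |
| 0.15 | 5.8% | 1.18 | 0.45 | 7.3% |
| 0.20 | 6.7% | 1.36 | 0.86 | 13.9% |
| 0.30 | 8.3% | 1.73 | 1.62 | 36.9% |

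Keep control uptake at 5% and change adoption among inclined women. At 15%, the ORs run from 1.12 to 1.48. At 30%, they run from 1.30 to 2.24; here the remaining women adopt at (0.05 − 0.03)/0.90 = 2.2%, a 13.5-fold contrast.

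**Illustration B (milder assumptions).** Half the women are receptive, with 2 or 3 times the uptake of the others, and control uptake is 5%, 7% or 16%.

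| Receptive share in one arm | Spurious OR | Rejection rate |
|---|---|---|
| 60% | 1.07–1.12 | 5.4–8.1% |
| 70% | 1.14–1.25 | 6.5–17.5% |
| 80% | 1.21–1.38 | 8.3–32.5% |

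**Reverse direction.** Take a true OR of 2.43 on 5%, which gives 11.34% in the intervention arm. In Illustration A, let the inclined share rise to 20% in the control arm instead. Observed control uptake is then 6.67%, and the OR is (0.1134/0.8866)/(0.0667/0.9333) = 1.79. By the same formula, power falls from 81% to 51%.

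**The case against.** Several links are inferred. No sentence places randomization before screening or consent, and none says that one person both recruits and counsels the same woman. The five assistants are named for Phase I; Phase II takes over the sampling method without restating the staffing. The article condenses a fuller protocol, which may fix the order of steps. All this stands, and it is why the point is that the arm is *knowable*, not that each recruiter certainly knows it from the first woman on.

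A reader might infer that women accept more readily in the intervention arm because of the workshop and its payment: "Participants who participate in the learning workshop will receive 20,000 UGX (equivalent to US$6) for transportation". The article does not support that. Women are invited to the workshop two weeks after enrollment and may decline. The payment is for transportation and goes to attendees only, and the incentive after the initial interview is the same for all. What women hear before they agree is not shown.

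The safeguards count for something. Systematic sampling removes the recruiter's choice of whom to approach, current dual-method users are excluded in both arms, and baseline items such as pregnancy intention, sexual history and condom self-efficacy would make some imbalance visible. None of these governs acceptance or the recording of eligibility.

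The analysis plan, if there is one, may name further covariates, and the article does not say whether Models 1 to 6 carry the arm term. That limits the modeling remark to what the article states.

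Finally, the larger odds ratios need strong assumptions. An OR of 1.73 needs the inclined share to triple and a six-fold difference in uptake. The 2.24 case needs a 13.5-fold difference. Nothing in the article supports either.

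**Conclusion.** The concern holds as a weakness of the described procedure: the facility's arm is knowable at recruitment for nearly all women, and nothing described stops acceptance or recorded eligibility from depending on it. The article does not show that bias will occur, or in which direction.

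Its size is unknown. Under the assumed inputs with no true effect, spurious odds ratios are mostly about 1.1 to 1.7, against a planned 2.43. A reader might infer that selective enrollment could by itself produce the planned effect; the calculations do not support that, since even the extreme 2.24 stays below it. They do show that the 5% error rate can be exceeded and that a true effect can be diluted. The upper values are comparable to the source study's estimate of 1.58. All of this rests on the assumed control rates, shares and uptake ratios given above. The change is worth making because it costs little.

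**What to change.** 1. Use the same neutral invitation wording in both arms, without arm-specific content. Complete screening, consent and the baseline interview before the woman is told what her facility offers. A script that describes both packages is not advised, because it would tell control women about the intervention and work against the plan's aim of limiting contamination.
2. Log the clients approached, eligible and consenting at each facility, and report these numbers by arm.
3. Include baseline condom-use frequency as a prespecified covariate in the primary mixed-effects model. This information is needed in any case to apply the dual-method exclusion.

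The cost is a common wording, a changed order of forms, a short facility log and one model term. The consent text must cover either arm without arm-specific detail, which the ethics committee would have to accept. Recruiters may still learn a facility's arm, so masking is partial, and the covariate corrects only measured imbalance. Separating recruiting from counseling staff would help where rosters allow, but Phase II staffing is not given, so the fix does not depend on it.
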